### Eligibility

Patients will be eligible for this study if:
Aged 16 years or over;

Patients with a fracture that involves the distal tibial metaphysis—defined as a fracture extending within 2 Müller squares of the ankle joint^21^—are eligible if:
The fracture is closed;In the opinion of the attending surgeon, the patient would benefit from internal fixation of the fracture.

Patients will be excluded from participation in this study if:
In the opinion of the attending surgeon, there is a contraindication to intramedullary nailing;The fracture is open;There is a contra-indication to anaesthesia;There is evidence that the patient would be unable to adhere to trial procedures or complete questionnairesThe fracture extends into the ankle joint (ie, intra-articular fracture).

Contraindications to intramedullary nailing are: the medullary canal is too narrow OR there is a preinjury deformity of the medullary canal OR it is not possible to achieve fixation of four cortices with screws distal to the fracture. We feel that these exclusion criteria will be easily understood by the surgeons and are in keeping with the pragmatic nature of the trial. However, we will include the specific reason in the trial screening data. For those patients withdrawing from the trial after written consent has been obtained, data obtained up until the point of withdrawal will be included in the final analysis.

### Recruitment

The internal pilot will specifically inform and test the recruitment rate for the main trial. Recruitment will take place in six trial centres over a period of 6 months. The expected rate of recruitment is based on a pre-pilot study performed at the lead centre. The average recruitment rate for this pre-pilot study, during which 24 patients were recruited, was 1.3 patients per month. The other centres involved in the trial will all be regional trauma units with similar catchment areas to the lead centre. Experience from previous multicentre trials has, however, shown that recruitment outside of the lead centre tends to occur at a lower rate. As such, a conservative recruitment rate of 0.75 patient per month per centre is estimated for this trial. If this recruitment rate can be achieved by the end of the internal pilot, the trial will progress to the main phase. We intend to recruit patients from a minimum of 18 centres in total (including the lead centre). The sample of 320 patients will be recruited over a 30-month period.

Screening logs will be collected throughout the trial to assess the main reasons for patient exclusion as well as the number of patients unwilling to take part. Patients will be screened by the Research Associates in the Emergency Department and Fracture Clinics at the trial centres. Any patient over 16 years of age, with a fracture of the distal tibia who, in the opinion of the treating surgeon, would benefit from internal fixation, will potentially be eligible for the trial. The trial will act in accordance with the Mental Capacity Act 2005 and the procedures for undertaking trials in ‘emergency settings’ will be followed as described in detail below in section 3.6.3 (consent) of this protocol. The consent procedures will be reviewed at the end of the pilot period.

### Consent

The clinical team responsible for patient care will make the decision regarding patient capacity. Informed consent from the patient will be obtained by the local research associate. Patients will be provided with verbal and written information about the study. In general, patients who are admitted with a fracture of the distal tibia will have their surgery on the next available trauma list. Timing and appropriateness of obtaining consent in this setting will be closely monitored during the internal pilot, and reviewed by the independent Trial Steering Committee.

For those patients withdrawing from the trial after written consent has been obtained, data obtained up until the point of withdrawal will be included in the final analysis.

Any new information that arises during the trial that may affect participants’ willingness to take part will be reviewed by the Trial Steering Committee; if necessary, this will be communicated to all participants. A revised consent form will be completed if necessary.

### Randomisation

The method of fixation will be allocated using a secure, centralised, web-based randomisation service. The randomisation service will be available 24 h each day to facilitate the inclusion of all eligible patients. The allocated treatment will then be reported to the research associate who will inform the treating surgeon. The surgeon will then arrange the allocated surgery on the next available trauma operating list, as per standard practice at that institution; this will ensure the integrity of the randomisation process. Randomisation will be implemented using a minimisation algorithm (sometimes referred to as *adaptive randomisation*) that attempts, at recruitment of each new patient, to balance the marginal totals for each level of the stratification factors identified below. This is the usual practice for trials run at Warwick clinical trials unit (CTU). Experience indicates that, for studies where some centres recruit only a relative small number of patients, this method tends to perform better than conventional stratification methods.

*Stratification by centre* will help to ensure that any clustering effect related to the centre itself will be equally distributed in the trial arms. The catchment area (the local population served by the hospital) will be similar for all of the hospitals, each hospital being a trauma unit dealing with these fractures on a daily basis. While it is possible that the surgeons at one centre may be more expert in one or the other treatment than those at another centre, all of the recruiting hospitals have been/will be chosen on the basis that both techniques are currently routinely available at the centre, that is, theatre staff and surgeons will already be equally familiar with both forms of fixation. This cannot eliminate the surgeon-specific effect of an individual at any one centre.^22^ However, fixation of a fracture of the tibia is not an uncommon procedure and many surgeons will be involved in the management of this group of patients: between 10 and 30 surgeons at each centre, including Consultants and Trainees. Therefore, we anticipate that each individual surgeon will only operate on 2–3 patients enrolled in the trial, greatly reducing the risk of a surgeon-specific effect on the outcome at any one centre.

*Stratification on the basis of age* will be used to discriminate between younger patients with normal bone quality sustaining high-energy fractures, and older patients with low-energy (fragility) fractures related to osteoporosis. The stratification will help to identify any effect related to the quality of the patients’ bone. The use of DEXA (dual-energy X-ray absorptiometry) is widely regarded as the gold standard for the assessment of bone density. However, such an investigation may be expensive and not routinely available at all centres.

Therefore, we propose to use age as a surrogate for bone density. In a large study in Norway, involving 7600 participants, it was demonstrated that bone mineral density remains stable up until the age of 50 years. After the age of 50 years, bone mineral density decreased steadily in males, while in females there was an initial decline between the ages of 50 and 65 years, with a further decline in both age groups thereafter.^23^ Over 1000 patients with a fracture were recently assessed in a study by Court-Brown and Caeser.^24^ This study confirmed that there is a clear bimodal distribution according to the age of the patient. The crossover of the two peaks of incidence was around 50 years of age. These studies provide strong evidence that patients over 50 years of age become increasingly vulnerable to fragility fractures. Therefore, we have chosen an age of 50 years as the stratification cut-off for this trial.

### Postrandomisation withdrawals

Participants may decline to continue to take part in the trial at any time and without prejudice. A decision to decline consent or withdraw will not affect the standard of care the patient receives.

Participants have two options for withdrawal:
Participants may withdraw from completing any further questionnaires but allow the trial team to continue to anonymously view and record any relevant hospital data that is recorded as part of normal standard of care; including X-rays and further surgery information.Or participants can withdrawal wholly from the study and only data obtained up until the point of withdrawal will be included in the final analysis of the study; thereafter no further data will be collected for that participant.

Once withdrawn, the patient will be advised to discuss their further care plan with their surgeon.

### Blinding

As the type of fixation used requires clearly visible surgical scars, the patients cannot be blind to their treatment. In addition, the treating surgeons will also not be blind to the treatment, but will take no part in the postoperative assessment of the patients. The functional outcome data will be collected and entered into the trial central database via questionnaire by a research assistant/data clerk in the trial central office. The X-rays collected will be reviewed by an independent assessor.

## Trial treatments

All the hospitals involved in this trial currently use both methods of fixation and all the consulting surgeons involved will be familiar with both techniques. Operative fixation of fractures of the distal tibia usually takes place under a general anaesthetic, but this decision will be made by the attending anaesthetist.

Each patient will undergo the allocated surgery according to the preferred technique of the operating surgeon. However, the basic principles of intramedullary nailing and ‘locking’ plate fixation are inherent in the technique (see below), there are several different implant systems and several different options for the positioning of the screws. Similarly, each surgeon will make minor modifications to their surgical technique according to preference and the specific pattern of each fracture. In this trial, the details of the surgery will be left entirely to the discretion of the surgeon, to ensure that the results of the trial can be generalised to as wide a group of patients as possible. However, a copy of the ‘operating record’ will form part of the trial data set.

Although all of the surgeons in the trial will be familiar with both techniques, it is possible that an individual surgeon may have more experience with one technique than the other. We expect that the proficiency of an individual surgeon to perform the procedure may change over time, as the surgeon gains experience and expertise. The term ‘learning curve’ is often used to describe this process. It will be important to monitor the learning curve for all surgeons throughout the trial. The operating time recorded on the operative record for each surgery will be used as a proxy to measure the task efficiency of the surgeons (quality assurance of the clinical process), and the number of complications (eg, infections) at 6 weeks after surgery will also be recorded as a patient-based outcome. Given the number of centres and surgeons taking part in this trial, no individual surgeon will perform more than a small number of the procedures. However, where data are available for individual surgeons, temporal variations in operation times and complications at 1 week will be modelled for each surgeon using a power curve for the trend, with appropriate adjustment for confounding factors such as the age of the patients.^22^ Also, as this study involves multiple surgeons, in addition to multiple centres, we anticipate that a more complex hierarchical model^16^ that fully accounts for the structure of the data may prove to be useful; we therefore anticipate fitting models of this type in the analysis. Results from the learning curve analysis for each surgeon will inform inferences regarding overall treatment differences and, if necessary, guide recommendations for implementation and training.

### Intramedullary nailing

The intramedullary nail is inserted at the proximal end of the tibia and passed down the centre (medullary canal) of the bone in order to hold the fracture in the correct (anatomical) position. The reduction technique, the surgical approach, the type and size of the nail, the configuration of the proximal and distal interlocking screws, and any supplementary device or technique, will be left entirely to the discretion of the surgeon as per standard clinical practice.

### ‘Locking’ plate fixation

The ‘locking’ plate is inserted at the distal end of the tibia and passed under the skin onto the surface of the bone. Again, the details of the reduction technique, the surgical approach, the type and position of the plate, the number and configuration of fixed-angle screws and any supplementary device or technique, will be left to the discretion of the surgeon. The only stipulation is that fixed-angle screws must be used in at least some of the distal screw holes—this is standard practice with all distal tibia ‘locking’ plates.

### Rehabilitation

We will ensure that all patients randomised into the two groups will receive the same standardised, written physiotherapy advice detailing the exercises they need to perform for rehabilitation following their injury. All of the patients in both groups will be advised to move their toes, ankle and knee joints fully within the limits of their comfort. Weight-bearing status will be decided by the treating surgeon. In this pragmatic trial, any other rehabilitation input beyond the written physiotherapy advice (including a formal referral to physiotherapy) will be left to the discretion of the treating clinicians. However, a record of any additional rehabilitation input (type of input and number of additional appointments) together with a record of any other investigations/interventions will be requested as part of the 3-month, 6-month and 12-month follow-ups, and this will also form part of the trial data set.

### Follow-up

Baseline, standardised radiographs will be copied from the hospital picture archiving and communication (PAC) system. Copies of the baseline clinical report forms (CRFs) and images will be delivered to the trial co-ordinating centre.

As part of routine clinical practice, patients will be seen in clinic on a regular basis after this injury. Any further clinical follow-up in the first year after the injury will be at the discretion of the surgeon, but will not influence the collection of the standard outcome data. For this trial, the primary outcome point will be at 6 months, when patients with an uncomplicated fracture may expect to return to normal activities; but to ensure that all complications and secondary procedures are captured, we propose to continue follow-up for 1 year.^13^

The research associate will perform a clinical assessment and make a record of any early complications at 6 weeks. Radiographs will be taken at 6 weeks and 12 months. The radiograph at 6 weeks will be used to assess the quality of the reduction: mal-alignment will be defined as more than 10 mm of shortening and more than 5° of angulation in any plane.^2^ An uncomplicated fracture of the distal tibia would be expected to be clinically united at 6 months after the injury. The primary functional outcome measure will therefore be collected at 6 months. However, radiographic union may lag behind the clinical picture. Therefore, the 12-month radiographs will be used as the definitive radiographic assessment of alignment^2^ and to assess if there are long-term complications, including non-union (failure to show bridging callus on three of four cortices on orthogonal radiographs) and arthritis of the ankle joint (joint space narrowing with osteophyte formation and peri-articular sclerosis).

The functional outcome data will be collected using questionnaires at 3, 6 and 12 months postoperatively. In addition to the DRI, the patients will be asked to fill out the EuroQol questionnaire, a complications/further surgical interventions and resource-use questionnaire. Patients will be asked to complete their 6-month and 12-month postoperative questionnaire during their routine follow-up appointments. The 3-month postoperative questionnaires, short annual questionnaires and any ‘missed’ questionnaires, will be sent to the patients through the post; a process carried out centrally by a data clerk at the Warwick Clinical Trials Unit. All the outcome questionnaires can be completed over the phone if postal copies are not returned. Text messages may be sent to patients to inform them that a questionnaire is due or on its way. Text messages will only be sent to those patients who have given their prior consent to this by initialling the corresponding box on the consent form. Text messages will be sent via the Warwick Clinical Trials Unit mobile phone from a secure office. The lead site (University of Warwick) will request a copy of the consent form from each patient entered into the study to determine if the patient has consented to text messages before a message is sent out.

Thereafter, patients who have consented to the ‘long-term’ follow-up will be sent an annual postal questionnaire for ongoing surveillance.

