## Background

The tibia is the most commonly broken major bone in the leg. Injuries usually require hospital admission and frequently require surgery, resulting in prolonged periods (months) away from work and social activities.

The treatment of displaced, extra-articular fractures of the distal tibia (lower third) remains controversial. These injuries are difficult to manage due to the limited soft tissue cover, poor vascularity of the area and proximity of the fracture to the ankle joint. Infections, non-union and mal-union, are well-recognised complications.

Non-operative treatment is one option and avoids the risks associated with surgery. Sarmiento *et al*,^1^ in 2003, reviewed 450 closed fractures of the distal tibial following functional bracing: 13.1% developed a mal-union (defined as >7° of angulation or 12 mm shortening). A further study using a more robust definition of 10 mm shortening and 5° angulation found a higher rate of mal-union (26.4%).^2^ Bostman *et al*^2^ treated patients using a long leg cast and failure to maintain reduction led to surgical treatment with an intramedullary nail. Thirty-two of 103 cases required nailing at a mean of 9 days following injury. Two patients in this group and three in the non-operative group went on to have a non-union.^2^ Union rates were faster with intramedullary nailing compared with conservative treatment—median values were 12.5 and 14.5 weeks, respectively (p<0.001).^2^ Digby *et al*^3^ also found that non-operative treatment for tibial fractures in the metaphyseal region leads to unacceptable deformity and ankle stiffness. Therefore, non-operative treatment is not the treatment of choice in the majority of patients with a fracture of the distal tibia.

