Surgical treatment options are expanding and include locked intramedullary nails, plate and screw fixation, as well as external fixator systems including the Ilizarov frame and hybrid fixators. External fixators may be beneficial in selected cases—particularly those with severe soft tissue injuries—but, in the UK, the nail and plate options are most commonly used for extra-articular fractures. Mid-shaft fractures of the tibia are generally successfully treated with locked intramedullary nails. However, in the more distal metaphyseal region of the tibia, the fixation may be less stable.^4^ The nail or screws that are inserted into the nail may break,^5^ mal-alignment may occur,^6^ and there is a risk that the nail will penetrate into the ankle joint.^7^
^8^

The development of ‘locking’ plates (where a thread on the head of the screws locks into the holes in the plate to create a ‘fixed-angle’ construct) has led to a recent increase in the use of plate fixation. However, plates are not without risks, they require greater soft tissue dissection, which carries a risk of infection, wound breakdown and devitalisation of the surrounding tissue.^9^

In a retrospective study of 111 patients with extra-articular fractures of the distal tibia (4–11 cm proximal to the plafond), a comparison was made between intramedullary nailing and plate fixation. Seventy-six fractures were treated with an intramedullary nail and 37 were treated with a medial plate.^10^ Nine patients (12%) had a delayed union or non-union in the intramedullary nail group and one patient (2.7%) had a non-union after plate fixation (p=0.10). Angular mal-alignment of ≥5° occurred in 22 patients with nails (29%) and 2 with plates (5.4%, p=0.003). The authors concluded that fractures of the distal tibia may be treated successfully with plates or nails, but that delayed union, mal-union and secondary procedures were more frequent after intramedullary nailing. Janssen *et al*^11^ found similar results, delayed union was higher in the intramedullary nail group (25%) compared to the plate fixation group (16.7%), rotational mal-alignment was also higher in the intramedullary nailing group (16.7%) compared with 0% in the plate group. However, this was not a randomised controlled trial (RCT) and the results do need to be interpreted with some caution. Randomised prospective assessment will be necessary to further clarify these issues and provide information about costs associated with these fractures.^10^

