## Objectives

The primary objective is:
 To quantify and draw inferences on observed differences in the DRI between the trial treatment groups at 6 months after injury.

The secondary objectives are:
To quantify and draw inferences on observed differences in early functional status at 3 months and later functional status at 12 months.To quantify and draw inferences on observed differences in the radiological outcomes: non-union, mal-alignment and shortening.To identify any differences in health-related quality of life between the trial treatment groups in the first year after injury.To determine the complication rate of intramedullary nail fixation versus ‘locking’ plate fixation in the first year after injury.To investigate, using appropriate statistical and economic analytical methods, the resource-use, costs and comparative cost-effectiveness of intramedullary nail fixation versus ‘locking’ plate fixation.

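### Mal-alignment is worded as shortening and angulation together, so a limb that is only angulated would count as aligned

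*Protocol article*

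**What the plan says.** The protocol article defines the outcome once, under Follow-up, where the 6-week film is used to judge reduction: "mal-alignment will be defined as more than 10 mm of shortening and more than 5° of angulation in any plane". The same section then says that "the 12-month radiographs will be used as the definitive radiographic assessment of alignment". It cites the same source and gives no second definition, so the one rule appears to govern both time points.

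Three other places bear on how it should be read:

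- Objectives names "the radiological outcomes: non-union, mal-alignment and shortening" as the subject of a secondary objective.
- Background describes two non-operative cohorts. For the first, mal-union is "defined as >7° of angulation or 12 mm shortening", with a rate of 13.1%. The second is the source cited for the trial's own limits. There the limits are 10 mm and 5°, again joined by *and*, and the rate is 26.4%.
- Background also reports a retrospective nail-versus-plate comparison that uses angulation alone: "Angular mal-alignment of ≥5° occurred in 22 patients with nails (29%) and 2 with plates (5.4%, p=0.003").

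Blinding says that an independent assessor will review the X-rays.

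**The concern.** With *and* read as a conjunction, a tibia with 15° of angulation and 9 mm of shortening is not mal-aligned. A limb that is short but straight can still be counted, because shortening is listed as its own radiological outcome. A limb that is angulated but not short has no named radiological outcome. Mal-union is recorded as a complication under Outcome measures, but the article attaches no criterion to it there.

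Angulation is also the deformity on which the retrospective study cited in the Background separated nail from plate. If the assessor applies the sentence as written, a stated secondary objective is answered with a count that omits angulation-only cases. If the assessor takes each limit as sufficient, the count differs. The text does not settle which, and a choice made after results are seen by arm would be open to challenge.

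**Working it through.** **1. The passages compared.**

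- *Objectives.* Listing mal-alignment beside shortening implies that a limb can be mal-aligned without being short. Under a both-required rule it cannot: every mal-aligned limb is also shortened by more than 10 mm. Under an either-suffices rule it can, although the two outcomes still overlap.
- *Background, non-operative cohorts.* Within one cohort, moving from 7° or 12 mm to 5° or 10 mm cannot lower the rate. Moving from 7° or 12 mm to 5° and 10 mm together carries no such guarantee and would usually lower it. The reported rate rises from 13.1% to 26.4%, which fits two limits each sufficient better. The cohorts differ (functional bracing v long leg cast), so this is suggestive only.
- *Background, retrospective study.* It uses angulation of 5° or more with no shortening condition. It describes another study's measure and does not define this trial's outcome.

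**2. The plan's own sample size.** Sample size gives a DRI difference of 8, SD 20, two-sided 5% and 90% power. Per arm, 2 × (1.960 + 1.282)² × 20² / 8² = 131.4, rounded up to 132, or 264 in total. This matches Table 2. The article states no sample size, event count or power for mal-alignment, so 132 per arm is borrowed here as the evaluable number.

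**3. What the literal rule could cost.**

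Inputs from the Background: 22/76 = 28.9% (nail) and 2/37 = 5.4% (plate), entered as 0.29 and 0.054. Assumption: a share f of angulated limbs is also shortened by more than 10 mm, equal in both arms. The article gives neither f nor a shortening rate.

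Rates under the both-required rule are p₁ = 0.29f and p₂ = 0.054f. Power is that of a two-sided 5% two-proportion test with pooled null variance, where p̄ is the mean of p₁ and p₂:

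Φ{ [p₁ − p₂ − 1.96 √(2p̄(1−p̄)/n)] / √([p₁(1−p₁) + p₂(1−p₂)]/n) }

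Example, f = 0.25 and n = 132: p₁ = 0.0725, p₂ = 0.0135, p̄ = 0.043. The two standard errors are 0.02497 and 0.02471. (0.059 − 0.0489)/0.02471 = 0.41, so power is about 66%.

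| f | Rates, nail v plate | Expected events, 132 per arm | Power |
|---|---|---|---|
| 1 (angulation alone) | 29% v 5.4% | 45.4 | above 99% |
| 0.75 | 21.8% v 4.1% | 34.1 | 99% |
| 0.50 | 14.5% v 2.7% | 22.7 | 93% |
| 0.25 | 7.3% v 1.4% | 11.4 | 66% |
| 0.10 | 2.9% v 0.5% | 4.5 | 31% |

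With 128 to 160 per arm, the f = 0.10 row gives 31% to 37% and the f = 0.25 row 65% to 74%.

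An either-suffices rule would count at least the angulation events, plus any limb with shortening alone.

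**The case against.** The best defence is that the sentence is loose drafting and harmless. The Background uses *and* for the same source beside the higher rate, so the authors may simply list two limits in this way. The outcome is secondary, no power is claimed for it, and both measurements come from films already planned, so the classification can be settled before analysis. All of that stands and lowers the severity. It does not remove the fault, because the assessor still has a definition whose plain meaning excludes isolated angulation.

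The evidence for a large effect is also thinner than one study suggests. The 29% v 5.4% is retrospective. The Background also cites a review of 1125 fractures, none from randomised trials, with similar mal-union rates for nail and plate. Risks and benefits says that no data point to greater risk in either group. The power figures illustrate loss of information at one cited effect and do not forecast this trial.

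A reader might further infer that the rule biases the comparison towards no difference. With the same f in both arms, the risk ratio stays at 0.29/0.054 = 5.4 whatever f is. The absolute difference and the precision fall, but the relative effect does not move. A shift in the risk ratio would need f to differ between arms, and the article says nothing on that.

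**Conclusion.** The definition is wrong as written for a stated secondary objective. Taken literally, it scores angulation-only deformity as aligned, and it does not fit the Objectives. The mal-alignment count can only be equal to or lower than the count by angulation alone. The power range, about 31% to 99% for f from 0.10 to 0.75 at 132 per arm, rests on the assumed f, on f being equal in both arms and on the rates of one retrospective study.

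A reader might infer that most events are lost. For angulation events that needs f below 0.5, which the article neither states nor allows one to derive. A reader might also extend the point to the whole radiological comparison. Non-union has its own definition, and isolated shortening is covered by its own listed outcome, so only isolated angulation is at risk. Nor does the article prove that *or* was intended. The primary DRI analysis and its 264 evaluable patients are untouched. Severity is minor to moderate.

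**What to change.** Before radiographic results are seen by arm:

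- Reword the Follow-up definition so that either limit suffices: more than 5° of angulation in any plane, or more than 10 mm of shortening.
- Reconcile it with the Background wording for the cited source and with the list in the Objectives.
- Report angulation and shortening as separate components as well. Under an either-suffices rule a short limb enters both mal-alignment and shortening, and the components keep that visible.
- State that the same rule applies to the 6-week and 12-month films.
- If both limits are truly required, say so, give the reason, and name isolated angulation as an outcome of its own.

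The cost is a wording change in the protocol, carried into any analysis plan and the assessor's instructions. No extra films are needed, since the present definition already requires both measurements. The primary analysis and the sample size do not change.
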